### 3.3. Withdrawal Criteria

Reasons for the participant to be discontinued from the study by the investigator:informed consent withdrawal,a less than 80% adherence to the study protocol-required product/placebo supplementation,non-attendance at the study visits,the lack of contact with the telephone interviewer,any exclusion criteria found after enrollment,any serious adverse event during the intervention period.

Participants may withdraw from the study at any time without any consequences. In such cases, their study intervention will be stopped and recorded as a “treatment failure”.

Reasons for withdrawal will be recorded by the investigator and saved for data analysis.

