### 3.2. Exclusion Criteria

Exclusion criteria will include:unclassified IBS;gastrointestinal conditions other than IBS, including clinical or endoscopic diagnosis of gastroenteritis, celiac disease, or inflammatory bowel disease;other diseases, such as respiratory disorders (asthma, chronic obstructive pulmonary disease); cardiovascular disorders, including uncontrolled hypertension (blood pressure > 170/100 mmHg); endocrine disorders, including diabetes mellitus (fasting blood glucose > 11 mmol/L) or thyroid diseases; severe neurological conditions, including psychosis; malignancy; and hepatic or renal impairment;unexplained blood biochemistry abnormalities: serum creatinine levels over twice the upper limit of normal, AST or ALT levels over twice the upper limit of normal;pregnancy or breastfeeding;hypersensitivity to soy or other food allergens;lactose intolerance;a surgical procedure scheduled during the course of the clinical study;the use of gastrointestinal motility stimulants or dietary fiber supplements during the two weeks preceding the clinical study;the use of antithrombotic drugs;current use of gut microbiota-targeted dietary supplements or drugs, such as probiotics, prebiotics, synbiotics, SCFAs, and a refusal to undergo a 1-month washout period;antibiotic therapy during the one month preceding the study;antibiotic use during the study;any drugs, except contraceptive pills or intramuscular contraceptives, hormone replacement therapy (estrogen/progesterone), L-thyroxine, antidepressants at low doses (up to 25 mg of amitriptyline, nortriptyline, or a selective serotonin reuptake inhibitor per day), antihypertensive drugs at low doses (diuretics, angiotensin-converting enzyme inhibitors, angiotensin receptor antagonists) and provided they have been used at a stable dose and for at least one month prior to the study;being included in another clinical study during the previous three months;a history of alcohol or substance abuse;COVID-19 infection, contact with any COVID-19-positive individuals during the previous two weeks.

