### 4.7. Telephone Interview

Telephone interviewers will call participants once a week to monitor study preparation intake and daily diary entries, and to collect data on side effects and the use of other medications, particularly antibiotics. Adverse events will be evaluated on a scale from 0 (no) to 1 (yes). Participants who take antibiotics will be withdrawn from the study.

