### 4.10. Statistical Analyses

#### 4.10.1. Sample Size Calculation

Based on the effects observed in the previous study, in which we used a similar probiotic and prebiotic combination, but without microencapsulated sodium butyrate, in IBS patients [27], we have estimated that a sample size of 35 participants per group would be required to reach clinical significance. With an estimated drop-out ratio of about 20%, the total sample size would need to be 80 participants, which would ensure 80% power to demonstrate significance with a *p*-value < 0.05. To further enhance the statistical power, the sample size was ultimately set to 60 participants/cases per group, with a total of 120 patients to be included in the study.

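### Removing randomised patients from the study, not only from the product, puts the week-12 IBS-SSS and IBS-QOL comparisons at risk of becoming selected completer comparisons

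*Protocol article*

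**What the plan says.** Section 3.3 (Withdrawal Criteria) opens its list with "Reasons for the participant to be discontinued from the study by the investigator". Besides withdrawal of consent, the list contains:

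- "a less than 80% adherence to the study protocol-required product/placebo supplementation";
- "non-attendance at the study visits,the lack of contact with the telephone interviewer";
- "any exclusion criteria found after enrollment,any serious adverse event during the intervention period".

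Section 4.7 (Telephone Interview) adds: "Participants who take antibiotics will be withdrawn from the study". Section 3.2 also lists "antibiotic use during the study" among the exclusion criteria, so antibiotics fall under the late-found exclusion rule of section 3.3 as well.

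After the list, section 3.3 says that participants may withdraw at any time, and continues: "In such cases, their study intervention will be stopped and recorded as a" treatment failure. It adds that reasons for withdrawal are kept for the analysis.

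Section 4.8 names IBS-SSS, IBS-GIS, IBS-AR and IBS-QOL as primary. Section 4.10.2 lists t-tests, repeated-measures ANOVA, Wilcoxon tests and, for percentages, Fisher's exact test. Section 4.10.1 allows for loss: "With an estimated drop-out ratio of about 20" per cent.

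**The concern.** The removal reasons arise after enrolment, most of them only once product-taking has begun, and several can depend on how the patient is doing. Someone who feels no benefit or tolerates the capsules badly is more likely to fall below 80% intake, skip a visit or stop answering calls. The text ends participation in the study, not merely use of the capsules, and describes no further outcome collection. Followed as written, the week-12 scores of patients removed before then would be lost.

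That differs from leaving analysis detail to an SAP. An SAP can define populations and missing-data methods, but it cannot recover scores that were not collected. If the arms lose different kinds or proportions of patients, a comparison of those who remain is no longer protected by randomisation, and it favours the arm that sheds more of its poor responders.

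**Working it through.** **1. Can each primary outcome absorb a removed patient?**

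- *IBS-AR* (section 4.3, yes/no): a treatment failure can be counted as No, and Fisher's exact test can then use all 120.
- *IBS-GIS* (section 4.2, 1 to 7): possible if dichotomised, for example at the document's own cut of above 4 for improvement.
- *IBS-SSS* (section 4.1, 0 to 500) and *IBS-QOL* (section 4.5, 34 to 170): a t-test or ANOVA needs a score, and treatment failure is not one. Classical repeated-measures ANOVA also needs complete visits.

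Illustration for IBS-AR, assuming 50% response among those who stay in both arms and removals counted as failures: 0.5 × (1 − removal rate) gives 40.0% v 40.0% at 20%/20% removal, 37.5% v 42.5% at 25%/15%, and 35% v 45% at 30%/10%. The label therefore matters where it can be applied.

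**2. The plan's own loss figure.** From 35 per group with 20% loss, 35/0.80 = 43.75, so 44 per arm and 88 in total (35 × 1.20 = 42 per arm, 84 in total). The stated 80 is not reproduced either way. This does not affect the present point, because the planned 60 per arm leaves 60 × 0.80 = 48, above 35.

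**3. Power is not the issue.** No effect size is given. Back-solving 35 per group at two-sided 0.05 and 80% power gives d = √(2/35) × (1.960 + 0.842) = 0.67. At that value power is 95.6% with 60 per arm and 90.7% with 48.

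**4. Bias with no true effect, correlation model.** Assume 20% loss in each arm, random in one arm. In the other, it follows a latent normal variable correlated r with a worse outcome. The mean shift among those who stay is r × φ(z₀.₈₀)/0.80 = r × 0.35 SD.

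- r = 0.3: 0.105 SD. Non-centrality = 0.105 × √(48/2) = 0.51; two-sided rejection 8.1%.
- r = 0.5: 0.175 SD. Non-centrality = 0.86; two-sided rejection 13.7%.

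**5. Bias with no true effect, gap model.** Let removed patients be worse than stayers by k SD. If this holds in both arms, the completer difference is k × (p_active − p_placebo). If it holds in the active arm only, it is k × p_active. The standard error is √(1/n_active + 1/n_placebo) after loss from 60 per arm.

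| Removed, active/placebo | k | Both arms: bias (rejection) | Active arm only: bias (rejection) |
|---|---|---|---|
| 20%/20% | 0.5 | 0 (5.0%) | 0.10 SD (7.8%) |
| 20%/20% | 1.0 | 0 (5.0%) | 0.20 SD (16.5%) |
| 25%/15% | 0.5 | 0.05 SD (5.7%) | 0.125 SD (9.4%) |
| 25%/15% | 1.0 | 0.10 SD (7.8%) | 0.25 SD (23.1%) |
| 30%/10% | 0.5 | 0.10 SD (7.7%) | 0.15 SD (11.3%) |
| 30%/10% | 1.0 | 0.20 SD (16.3%) | 0.30 SD (30.8%) |

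The arm-specific rates, r and k are all assumptions. The document gives only about 20% overall, as an allowance for drop-out from any cause and not as the expected yield of these rules.

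**The case against.** A reader might infer that every listed test can use only those who remain, so that the trial's whole result is a completer analysis. The document does not support that. Fisher's exact test can include treatment failures, scores taken before removal stay usable at those visits, and no completer or per-protocol set is declared. Analysis populations and missing-data handling may stand in a fuller document that is not shown, so their absence is not held against the plan.

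Other points on that side also stand in part:

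- The article does not say when 80% adherence is judged. If it is judged only at the end, week-12 data may already exist. Non-collection is the natural reading of discontinuation from the study, not a stated fact.
- Patients who miss visits or cannot be reached are often missing whatever the rule says, so a change recovers only part of the loss.
- The treatment-failure sentence might be read across all of section 3.3, since withdrawal of consent also appears in the investigator's list. That reading is possible but unsettled.
- A reader might infer that safety data are cut off at a serious adverse event. Section 4 collects adverse events over the whole trial and section 4.9 requires reporting within 24 h, so the event itself is captured. Only follow-up after removal is left unaddressed.
- With equal loss and equal selection in both arms, the bias is nil.

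None of this gives IBS-SSS or IBS-QOL a value for a patient removed before week 12.

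**Conclusion.** The concern holds in a limited form. Sections 3.3 and 4.7 tie leaving the study to post-randomisation behaviour and events, and the one label offered for withdrawals has uncertain scope and no meaning on two of the four primary scales. The week-12 IBS-SSS and IBS-QOL comparisons are therefore at risk of being selected completer comparisons. That is a risk created by a stated rule, not a declared analysis.

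Under the assumptions shown, the bias runs from zero (same loss and selection in both arms) to about 0.10 to 0.18 SD, with rejection of about 8% to 14%, when 20% loss is outcome-related at r = 0.3 to 0.5 in one arm only. Unequal loss with a large outcome gap gives more. The larger sample size does not protect against it. It should be settled before patients are lost, because uncollected outcomes cannot be restored at analysis.

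**What to change.** 1. Separate stopping the product from leaving the study. Which events stop the product remains a clinical matter for the sponsor.
2. Keep every randomised patient who has not withdrawn consent in the planned weekly calls, diary and visits to week 12.
3. Analyse all randomised patients in their assigned arm with all collected data, for example with a likelihood-based mixed model for IBS-SSS and IBS-QOL. Such a model assumes data missing at random, so continued follow-up is the essential step.
4. State that treatment failure applies to every withdrawal reason and counts as non-response for IBS-AR and dichotomised IBS-GIS where no week-12 response is observed. Observed responses should not be overwritten, or the continued follow-up would serve no purpose for these outcomes.
5. Report the set with at least 80% adherence only as a sensitivity analysis.
6. Reconcile section 3.2 with sections 3.3 and 4.7 on antibiotics: use during the study cannot be judged at eligibility.

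The cost is a wording amendment and continued use of contacts already scheduled. The downside is some dilution of the estimate by non-adherent patients.

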## 4. Detailed Procedures

The following measurements will be performed:A physical examination—at each visit;Anthropometric measurements, including weight, height, body mass index (BMI), waist-to-hip ratio (WHR), and arm or calf circumference—at visit 0 and at weeks 4 and 12 of the study intervention;Nutritional status assessment and body composition analysis, including skin fold measurements and bioelectrical impedance analysis (BIA) with the use of a Bodystat machine—at visit 0 and at weeks 4 and 12 of the study intervention;IBS symptom severity assessment, with the use of IBS-SSS [32]—at visit 0 and at weeks 4, 8, and 12 of the study intervention, and with patient-rated (on a Likert scale) symptom severity from patient diaries—weekly;Improvement or worsening of IBS symptoms, with the use of the IBS-SSS, IBS-Global Improvement Scale (IBS-GIS), and IBS—Adequate Relief (IBS-AR) [33]—at weeks 4, 8, and 12 of the study intervention;Adverse events based on the data from telephone interviewers and obtained by the investigators during the whole trial;Quality of life (QOF) assessment, with the use of IBS-QOL questionnaire [34]—at visit 0 and at weeks 4 and 12,Laboratory tests (including complete blood count; liver function tests (ALT, AST); bilirubin, amylase, creatinine, C-reactive protein, glucose, and electrolyte levels at the screening visit; and cytokine (interleukin 6 (IL-6) and macrophage inflammatory protein 1β (MIP-1ß)) levels at visit 0 and at weeks 4 and 12 of the study intervention.

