## Abstract

Irritable bowel syndrome (IBS) is a functional gastrointestinal disease in the pathogenesis of which gut dysbiosis may play an important role. Thus, probiotics, prebiotics, or microbiota metabolites, such as butyric acid, are considered to be effective therapy for IBS. However, there are still no trials presenting the efficacy of these three biotic components administered simultaneously. This study aims to evaluate the effects of the product comprising sodium butyrate, probiotics, and short-chain fructooligosaccharides (scFOS) on the severity of clinical IBS symptoms and the quality of life (IBS-QOL). This is a randomized double-blind placebo-controlled trial conducted in 120 adults with IBS diagnosed according to Rome IV criteria. The intervention group (n = 60) will receive a mixture of the following components: 300 mg of colon-targeted microencapsulated sodium butyrate combined with probiotic *Lactobacillus* strains (*L. rhamnosus* and *L. acidophilus*) and *Bifidobacterium* strains (*B. longum*, *B. bifidum*, *B. lactis*), and 64 mg of prebiotic scFOS. The control group (n = 60) will receive a placebo (maltodextrin). The primary outcomes will be changes in IBS symptoms with the use of the IBS-Severity Scoring System (IBS-SSS), IBS-Global Improvement Scale (IBS-GIS), IBS-Adequate Relief (IBS-AR), and IBS-QOL after 12 weeks of intervention. The secondary outcomes will be the type of stools, patient-recorded symptoms, adverse events, anthropometric and nutritional parameters, and inflammatory cytokine levels. The findings will provide the first evidence of the use of a combination of three biotic compounds in IBS. The study was registered in the clinicaltrials.gov registry under the number NCT05013060.

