### 2.2. Study Design

This study will be a prospective, randomized, double-blind controlled trial. One hundred twenty patients from the outpatient clinic at the Gastroenterology Department of the Medical University of Lodz (Poland) will be enrolled in the study. The intervention group (n = 60) will receive the study product containing a mixture of microencapsulated butyric acid, probiotic *Lactobacillus* and *Bifidobacterium* strains, and prebiotic scFOS. The control group will receive a placebo—maltodextrin. The duration of the intervention will be 12 weeks. The study schedule will include five visits: the screening visit, whose purpose is to qualify patients to be enrolled in the study, the baseline visit after up to two weeks after the screening visit, at which participants will be randomized either to the intervention or placebo group, and three follow-up visits (after a 1-week run-in period) at weeks 4, 8, and 12 ± 3 days after the start of the intervention. The visit after eight weeks of intervention will be a phone visit by a researcher, the remaining visits will take place at the clinic. The study protocol diagram is presented in Figure 1.

Once recruited, the participants will receive a diary to fill out on a daily basis. Participants will also be monitored by interviewers via phone every week of the study. The study products will be provided to participants at the baseline visit and at the week 4 visit. At the baseline visit, the participant will be asked not to take the product during the first week (a 7-day run-in period) and to make daily patient-diary entries (containing information about the number and type of stool and the severity of specific IBS symptoms); on the seventh day, a telephone interviewer will instruct each participant to take the study product from the next day onwards.

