### 4.3. IBS-AR

IBS-AR is a dichotomous single-item questionnaire that asks participants “Over the past week, have you had adequate relief of your IBS symptoms?” The answer can be YES or NO.

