### 4.8. Study Endpoint Definition

The prospective defined primary efficacy outcome will be changes in IBS symptoms and quality of life measured with the use of the IBS-SSS, IBS-GIS, IBS-AR, and IBS-QOL questionnaires.

Secondary efficacy variables will include:the number and type of stools assessed with the BSF scale,pain, bloating/abdominal distension, stool urgency, feeling of incomplete evacuation after a bowel movement assessed with a patient-rated Likert scale,adverse events,anthropometric measurements and BMI,body composition,cytokine (IL-6, MIP-1ß) levels.

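### IBS-AR, one of four primary instruments, is asked in only 3 of 12 treated weeks, and on the abstract's reading one week's yes/no answer forms the result, although patients are telephoned every week

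*Protocol article*

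**What the plan says.** - **Item.** Section 4.3 gives a single yes/no question, "Over the past week, have you had adequate relief of your IBS symptoms". Its recall period is one week.
- **Schedule.** Section 4 lists "IBS—Adequate Relief (IBS-AR) [33]—at weeks 4, 8, and 12 of the study intervention". No IBS-AR at visit 0 is listed. The same section schedules "IBS-SSS [32]—at visit 0 and at weeks 4, 8, and 12 of the study intervention", so IBS-SSS does have a pre-treatment value.
- **Status.** Section 4.8 defines the primary efficacy outcome as "changes in IBS symptoms and quality of life measured with the use of the IBS-SSS, IBS-GIS, IBS-AR, and IBS-QOL questionnaires". It names no time point.
- **Time point.** The abstract lists the same four instruments and ends with "IBS-QOL after 12 weeks of intervention".
- **Treatment period.** Section 2.2 states "The duration of the intervention will be 12 weeks".
- **Contacts already planned.** Section 4.7 states "Telephone interviewers will call participants once a week to monitor study preparation intake and daily diary entries", and also covers side effects and other medication. Section 2.2 adds a call on day 7 of the product-free run-in. The relief question is not listed for these calls or for the daily diary in section 4.6.
- **Test.** Section 4.10.2 assigns Fisher's exact test to percentages, with a significance threshold of 0.05.

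**The concern.** A yes/no answer about one week is a coarse measurement of a condition whose defining pain the protocol describes as recurrent. If the week-12 answer alone is the result, a patient with relief in most treated weeks but a poor last week counts as a failure, and the reverse case counts as a success. That noise lowers power on a primary instrument.

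The recall window would fit a weekly question, and the trial already pays for a weekly call. This is a matter of data collection, so it cannot be deferred: a later analysis plan can decide how to combine three answers, but it cannot recover the weeks in which nobody asked.

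**Working it through.** **1. Coverage.** Three one-week windows in 12 weeks is 3/12 = 25% (21 of 84 days). Week 12 alone is 1/12 = 8.3%.

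**2. Inputs.** The plan has no power figure for IBS-AR to reproduce, because section 4.10.1 gives no relief rates.
- From the plan: 60 per group, about 20% drop-out, hence 60 × (1 − 0.20) = 48 evaluable per group; two-sided 0.05.
- Assumed: weekly relief 35% vs 60%, or 30% vs 50%; the same effect in every week; latent within-patient correlation 0.4 to 0.8, plus one scenario at 0.4 with adjacent-week autocorrelation of 0.6.

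**3. Week 12 alone, by hand.** Power ≈ Φ(Δ/SE − 1.96), with SE = √{[p₁(1−p₁) + p₂(1−p₂)]/n}.
- 35% vs 60%: SE = √[(0.2275 + 0.24)/48] = 0.0987. Then 0.25/0.0987 = 2.53, and Φ(0.57) ≈ 0.72.
- 30% vs 50%: SE = √[(0.21 + 0.25)/48] = 0.0979. Then 0.20/0.0979 = 2.04, and Φ(0.08) ≈ 0.53.

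These match the simulated t-test. Fisher's test is more conservative and gives less.

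**4. Why pooling helps.** The mean of k weekly answers with pairwise correlation r has its variance multiplied by [1 + (k−1)r]/k. Take r = 0.4 on the yes/no scale, roughly a latent correlation of 0.6, since (2/π)·arcsin(0.6) ≈ 0.41 at a 50% rate. For 35% vs 60%:
- k = 3: (1 + 0.8)/3 = 0.60. SE = 0.0987 × √0.60 = 0.0765, and Φ(3.27 − 1.96) ≈ 0.90.
- k = 12: (1 + 4.4)/12 = 0.45. SE = 0.0987 × √0.45 = 0.0662, and Φ(3.78 − 1.96) ≈ 0.97.

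**5. Simulation, 48 per arm, all correlation scenarios.**

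| IBS-AR result | 35% vs 60% | 30% vs 50% |
|---|---|---|
| Week 12 alone, Fisher | 61-64% | 43-46% |
| Week 12 alone, t-test | 69-72% | 51-53% |
| Weeks 4, 8, 12 pooled, t-test | 84-94% | 67-80% |
| All 12 weeks pooled, t-test | 89-99% | 73-94% |

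A repeat run for this write-up agreed to within about a percentage point.

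**6. Where the gain comes from.** On the t-test rows, pooling the three planned answers moves 69-72% to 84-94%. Asking weekly moves that to 89-99%, a further 5 points at each end. For 30% vs 50% the weekly step adds 6 to 14 points.

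**7. Which weeks.** A window of weeks 9-12 only is not clearly better than the planned weeks. For 35% vs 60% at latent correlation 0.4 with adjacent-week autocorrelation of 0.6, weeks 9-12 give about 89% and weeks 4, 8 and 12 about 92%. All 12 weeks gives about 97%.

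**8. Sensitivity to a cut-off.** With 40% vs 60%, latent correlation 0.3 to 0.7 and 48 per group, week 12 alone gives about 50%. Relief in at least 2 of the 3 planned weeks gives 57-70%, and in at least 6 of 12 weeks 63-88%. Analysing the proportion itself gives 69-84% for three weeks and 78-98% for twelve. The week-12 answer disagrees with the 6-of-12 status in about 16% to 28% of patients.

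**The case against.** **Does one week decide the result?** A reader might infer this, but the documents do not settle it. Three answers are scheduled, section 4.8 names no time point, and the abstract's phrase may only mark the end of the intervention period. A rule for combining the answers is commonly left to an analysis plan, so its absence is not the criticism. This objection stands: the low power for week 12 applies only on the abstract's reading.

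**Is it impossible to compute a change?** A reader might also infer this, because section 4.8 speaks of changes and there is no pre-treatment IBS-AR. The documents do not support it. Adequate relief is itself a judgement of change, and section 4 lists the item among measures of improvement or worsening, beside IBS-GIS, which also has no baseline. Fisher's test compares yes-proportions between randomised arms without one. Only a change from baseline is unavailable, and the comparison does not need it.

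**Is sparse sampling the real cause?** Largely not. Most of the power returns once the three planned answers are pooled. What survives is that twelve weekly answers gave the highest power in every scenario examined.

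**Is fluctuation covered elsewhere?** Partly. The diary gives weekly symptom severity and IBS-SSS has four assessments, so IBS-AR does not decide the trial. Neither records adequate relief.

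**Conclusion.** The point holds in a limited form. A primary instrument with one-week recall covers a quarter of the treated weeks. If the abstract's time point is taken literally, it uses one twelfth of them. Under the assumed rates, that use has 61-64% or 43-46% power by the test the protocol names for percentages, below the 80% in section 4.10.1 in both cases. Pooling the planned answers recovers most of the loss, and weekly collection recovers more.

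The sizes rest on assumed relief rates, assumed correlations and an effect that is constant over time; the documents give none of these. Part of the gap between the Fisher row and the pooled rows reflects the change of test, so the t-test rows are the fair comparison. This is a cheap improvement worth making, not a flaw that makes the trial uninterpretable.

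**What to change.** 1. Add the section 4.3 question to the existing weekly call for treated weeks 1 to 12, and amend sections 4, 4.3 and 4.7.
2. In section 4.8, define the IBS-AR result as each patient's proportion of treated weeks with adequate relief, compared between arms. Keep the week-12 answer as supportive.
3. State in section 4.10.2 that this proportion is analysed as a numeric variable, so that Fisher's test for percentages is not applied to it.
4. If weekly collection is not adopted, pool the answers from weeks 4, 8 and 12 instead of using week 12 alone. This needs no new data.
5. A run-in answer at the day-7 call is optional. Its gain as a covariate is probably small, because entry requires an IBS-SSS above 175 and few patients may report relief before treatment.

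The cost is one yes/no question per call and a few wording changes. The downsides are slightly longer calls, some missing weekly answers, and possible dilution by the early weeks if the effect appears late.
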